#### Physical activity

The primary outcome will be measured physical activity over a one-week period prior to the intervention (Time 1) and for a further week immediately post-intervention at the three-month follow-up occasion (Time 2) using accelerometers (GENEActiv Ltd.) [47, 67]. Participants will be asked to wear the unit continuously for the seven day period on the non-dominant upper arm to comply with hospital hygiene regulations. The GENEActiv device is water proof and participants will be informed that they are free to choose whether to wear it while swimming, showering, or sleeping. Data will be collected at 60 Hz epoch frequency. Step counts will be derived from the acceleration data using open-source macros and they will be used as proxy for physical activity [47]. Participants will be supplied with a band specifically designed to fasten the monitor to the upper arm.

Secondary outcomes will be assessed at baseline (Time 1) and post-intervention (Time 2), and will include subjective measures of physical activity, sitting time, sleep, depression, anxiety, stress, quality of life, theory-derived correlates of physical activity and self-reported weight. Demographics, perceived neighbourhood environment, personal need for structure, internet self-efficacy, and planning skills/ability will be assessed at baseline (Time 1) only. Secondary outcomes assessed only at the post-intervention stage (Time 2) will include measures of intervention accessibility, usefulness and satisfaction with the intervention, as well as acceptability of the advice provided. Participants’ website usage (e.g., time spent on pages with specific intervention content, number of website visits) will be assessed throughout the study using Google Analytics.

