### Study hypotheses

We hypothesise significant increases in physical activity between baseline and 3-month follow-up in the three intervention conditions but no change in physical activity levels in the control groupWe hypothesise that increases in physical activity at 3-month follow-up will be greatest in the habit intervention condition with smaller changes for the self-regulation and motivation conditions.We hypothesise that participants allocated to the habit condition will have maintained the physical activity changes over time relative to the self-regulation, motivation, and control conditions at 3-month follow-upWe hypothesise that higher engagement in the program (e.g., frequency of logins, number of sessions completed, reported relevance and usefulness of the sessions content) will lead to greater change in physical activity at 3-month follow-up in all intervention groups.We hypothesise that the effects of the habit condition on physical activity behaviour will be mediated by the self-reported habit development, effects of the self-regulation condition will be mediated by self-efficacy and planning, and the motivation condition will be mediated by the social cognitive variables of attitudes, motivation, and intention.

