### Study analysis

The intervention will be evaluated following the recent guidance on process evaluation for complex interventions [86]. Data will be analysed using generalized linear mixed modelling (GLMM) [87] with a 4 (condition: control, motivation, self-regulation, habit) × 2 (time: baseline, 3-month follow-up) mixed-model design, accounting for nesting within hospital. Models will be conducting to compare change between conditions of the primary outcome (physical activity) and secondary outcomes (e.g., theory-derived psychological constructs, DASS21, MOS-SF12, and absenteeism). Mediation analyses will be conducted using path analytic models using Preacher and Hayes’ bootstrapped approach for multiple mediation [88]. Separate path models will be conducted for each condition. Each condition will be represented by a dichotomous dummy-coded variable (0 = did not receive intervention component, 1 = received intervention component). Each condition variable will be set as a predictor of physical activity at follow up with motivation and intention (motivation condition), perceived behavioural control and planning (self-regulation condition), and self-reported habit (habit condition) as multiple mediators in each analysis, respectively. Baseline physical activity will be included as a control variable. Intention-to-treat (baseline carried forward) will be utilised for missing data from drop-out. Other missing data will be imputed using multiple imputation with chained equations [89]. Both intention-to-treat and completers analyses will be reported.

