In addition, the current study will focus on testing theoretically-distinct groups of techniques and their additive effects on health behavior change. The findings of the study will enable us to evaluate the potential mechanisms by which BCTs derived from motivation, volition and habit theories affect change in health-related behaviour. Our research will also enable us to test the mediators of the intervention effects to increase participants’ physical activity and quality of life, and to reduce work-related stress and absenteeism. We will be able to do this by comparing the effects of each intervention component (e.g., self-regulation) on outcomes mediated by specific theory-based psychological constructs (e.g., planning, self-efficacy) conceptually related to the component.

Personal characteristics of the intervention participants will be assessed to determine for whom the different intervention content is most suitable. Potential moderators of intervention effects will include level of engagement in the program and planning skills. Determining the characteristics of potential users will enable the future matching of participants with the most suitable intervention content. In addition, by providing opportunity for participants to report on the usability of the platform in healthcare professionals, we will be able to ascertain the extent to which the online intervention is feasible in this population and whether it would likely be used by the target population if it were rolled-out on a large scale.

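### The mediation models name baseline activity, but not the mediator's own baseline, as a covariate; run that way on follow-up mediators, they can take stable differences between people for mediation and lose precision

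*Protocol article*

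**What the plan says.** All references are to the protocol article.

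- **Method (Study analysis):** "Mediation analyses will be conducted using path analytic models using Preacher and Hayes’ bootstrapped approach for multiple mediation".
- **Exposure and outcome (Study analysis):** each component is coded "0 = did not receive intervention component, 1 = received intervention component", and "Each condition variable will be set as a predictor of physical activity at follow up". The mediators are motivation and intention, perceived behavioural control and planning, and self-reported habit, in separate models.
- **Covariate (Study analysis):** "Baseline physical activity will be included as a control variable". No other covariate is named for these models.
- **Hypothesis (Study hypotheses, fifth):** "the effects of the habit condition on physical activity behaviour will be mediated by the self-reported habit development".
- **Data available (Measures):** under Physical activity, "Secondary outcomes will be assessed at baseline (Time 1) and post-intervention (Time 2"), and the theory-derived correlates of activity are in that list. Table 3 shows the theory-relevant determinants, the intention items and the automaticity index at both times.
- **Purpose (Discussion):** "Our research will also enable us to test the mediators of the intervention effects".

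**The concern.** An indirect effect is the product of two paths: condition to mediator (a) and mediator to activity (b). Randomisation protects a. It does not protect b, which compares people who differ in the mediator for any reason.

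One accelerometer week measures usual activity imperfectly, so adjusting for it leaves some stable difference between people. Those who were always more motivated or more habitual tend to score high on the mediator and on follow-up activity, even if moving the mediator does nothing. Path b is then above zero for a reason unrelated to the intervention. If the arm also shifts the mediator, the product a × b can test as significant.

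Path a also keeps between-person variance that the mediator's own baseline would remove, which costs power when mediation is real. At stake is the explanation of how the intervention works, which the Discussion and Implications sections treat as a main contribution of the trial.

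**Working it through.** **Inputs from the article.** 134 participants required, 30% dropout, 192 recruited (48 per arm), d = 0.28 for activity (Sample size). The article gives no power figure for mediation. The one related step reproduces: 134 / 0.70 = 191.4, rounded up to 192. So 134 is used here as the number of completers. Whether 134 follows from d = 0.28 is a separate matter on which this point does not rest.

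**Assumptions, not in the article.** Stability (baseline to follow-up correlation) of the mediator, s_M = 0.3, 0.5 or 0.7; of activity, s_P = 0.7; correlation c between mediator and activity at all times, 0 to 0.3; mediator shift a in SD units; one mediator per model.

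**Step 1: group sizes.** If a component counts as received in every arm that contains it, the dummies split 192 as 144 v 48 (motivation), 96 v 96 (self-regulation) and 48 v 144 (habit). For 134 completers, the equal split is 67 v 67 and the quarter split about 34 v 100.

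**Step 2: path a.** SE = √[(1/n1 + 1/n0) × v], power = Φ(a/SE − 1.96). Without the baseline mediator v = 1; with it v = 1 − s_M². For a = 0.28:

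| Split | no baseline mediator | s_M = 0.3 | s_M = 0.5 | s_M = 0.7 |
|---|---|---|---|---|
| 67 v 67 | 37% | 40% | 46% | 62% |
| 34 v 100 | 29% | 32% | 37% | 51% |

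**Step 3: path b when the mediator has no effect.** Solving the normal equations within arms:

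- adjusting for baseline activity only: b = c(1 − s_P)/(1 − c²) = 0.3 × 0.3/0.91 = 0.099
- adding the baseline mediator: b = c(1 − s_P)/(1 + s_M − 2c²) = 0.09/1.52 = 0.059

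The true value is 0, so the addition reduces the bias but does not remove it. With c = 0.1 the two values are 0.03/0.99 = 0.030 and 0.03/1.68 = 0.018, both small.

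**Step 4: chance that both paths are significant (67 v 67, c = 0.3, stabilities 0.7).** The residual variance of the mediator is 0.91 as written and 0.501 with its baseline added; that of activity is about 0.50 in both.

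- Path b as written: 0.099/√(0.50/(134 × 0.91)) = 1.54, significant in 34% of trials. With the baseline mediator: 0.059/√(0.50/(134 × 0.501)) = 0.69, significant in about 11%.
- Path a at 0.5 SD: 86% as written, 98% with the baseline mediator. At 0.28 SD: 40% and 63%.
- Products: at 0.5 SD, 0.86 × 0.34 = 29% against 0.98 × 0.11 = about 10%; at 0.28 SD, 0.40 × 0.34 = 13% against 0.63 × 0.11 = 7%.

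**Step 5: simulation of false mediation** (percentile bootstrap 95% interval for a × b, true b = 0, N = 134, equal split, stabilities 0.7; Monte Carlo error about 1 to 2 points):

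| c | mediator shift | as written | baseline mediator added |
|---|---|---|---|
| 0.3 | 0.5 SD | 26-30% | 11-15% |
| 0.3 | 0.28 SD | 11-13% | 5-6% |
| 0.3 | none | 1% | under 1% |
| 0.1 | 0.5 SD | 6-7% | 7-8% |
| 0 | 0.5 SD | about 4% | about 6% |

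In a separate set of runs with baseline carried forward for 30% of 192 participants and a = 0.5, the figures are 16-19% against 7-8%.

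**Step 6: simulation of power for real mediation** (N = 134, equal split, a = 0.4, b = 0.3):

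| s_M | c | activity depends on | as written | baseline mediator added |
|---|---|---|---|---|
| 0.7 | 0 | mediator change, M2 − 0.7 × M0 | 37-41% | 79-84% |
| 0.7 | 0 | follow-up mediator level | 64-65% | 79-83% |
| 0.7 | 0.3 | mediator change, M2 − 0.7 × M0 | 66-68% | 88-90% |
| 0.5 | 0 | either form | 59-64% | 70-76% |
| 0.3 | 0 | mediator change, M2 − 0.3 × M0 | 68% | 70-72% |

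The gain is not universal. With 96 v 96, a = 0.5, b = 0.2, stability 0.7 and correlation 0.3, power fell by 3 points (87.5% to 84.5%).

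**The case against.** The strongest reply is that the article is condensed and does not settle the model. It attaches the follow-up time point to physical activity, not to the mediators. It does not say that its covariate list is complete, and its wording of the habit hypothesis fits a change measure. A reader might infer that no mediation model will use the Time 1 mediator values. The text does not support that: it only fails to name them. This limit stands, and it is why the point is conditional on the models being run as written with follow-up mediators. It does not dispose of the point. The article fixes method, coding, outcome, mediators and a covariate, and the covariate it names is the less useful of the two baselines for path a.

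A second reply concerns size, and it also stands. The lowest planned power (37-41%) arises at c = 0, where false mediation is about 4%. The inflated false mediation arises at c = 0.3, where planned power is 66-68%. The two harms should not be quoted as if they held at full size together. A shift of 0.5 SD is also large in a trial planned on 0.28 SD for activity, although the mediators are the more direct target of the intervention.

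Third, the remedy leaves residual bias, because b stays observational. Fourth, mediation is the fifth hypothesis; the primary comparison does not use these models, and change in the theory-derived constructs is compared separately in the mixed models. Both are true. They bear on the weight of the point, not on its direction.

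**Conclusion.** The point holds in a limited form. As written, the path models name baseline activity and leave out a baseline mediator that the trial collects. On follow-up mediators, this biases path b when mediator and activity share stable differences between people, and it makes path a less precise.

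The consequence ranges from nothing to substantial. False mediation is not inflated if the arm does not move the mediator, and hardly at all if the correlation is about 0.1 or less. At stability 0.7, correlation 0.3 and an equal split of 134, it is roughly twice as frequent as with the adjustment. Power for real mediation usually rises with the adjustment: by roughly 15 to 45 points at stability 0.7, by 10 to 15 at 0.5, and by a few points at 0.3. The article gives none of these stabilities, correlations or shifts.

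A reader might go further and conclude that the test will declare any questionnaire score it moves to be the mechanism, or that it always has far less power than the data allow. Neither follows: the first depends on the correlation and the size of the shift, the second on mediator stability and on how the mediator acts. The matter is worth correcting because the correction is nearly free and mechanism is a stated aim.

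**What to change.** In Study analysis, replace the covariate sentence for the mediation models with: *Baseline physical activity and the baseline (Time 1) value of each mediator in the model will be included as covariates in both the mediator and the outcome equations.*

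This also settles the open question of scoring: once the Time 1 value is in both equations, a follow-up score and a change score give the same a and b. Add that the mediator-to-activity path remains observational, because the adjustment reduces but does not remove confounding.

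The cost is one degree of freedom per mediator and no new data. Some mediation results may look less favourable. If the full analysis plan already contains these covariates, only the published description needs aligning.

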### Sample size

Reviews of behavioural intervention studies have reported small to medium effects of web-delivered interventions aimed at increasing physical activity [84, 85]. Studies that excluded participants who are already active, which most closely represent the current protocol, reported a small-to-medium effect (*d* = 0.28) [84]. Therefore, to detect a similar effect on physical activity between intervention and control group, a total of 134 participants will be required to achieve 80% power with alpha set at *p* < .05. Based on an estimated drop out of 30% from web-based tailored interventions to increase physical activity [84], the final target sample size of 192 participants (48 per group) will be recruited at baseline. The study is powered to detect differences between the intervention group and control group (i.e., parallel 2-arm trial); not between the four study arms.

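### Carrying baseline forward fixes the change of an expected 30% of participants at zero on an unsupported assumption, so the estimated effect is shrunken or biased unless dropouts truly stay at baseline

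*Protocol article*

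**What the plan says.** The Study analysis section of the protocol article plans a generalised linear mixed model with four conditions and two time points, comparing change between conditions. For dropout it fixes this rule: "Intention-to-treat (baseline carried forward) will be utilised for missing data from drop-out". Multiple imputation by chained equations is kept for other missing data. The section ends: "Both intention-to-treat and completers analyses will be reported". It does not say which of the two is primary.

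The Sample size section takes its effect from earlier studies that "reported a small-to-medium effect (*d* = 0.28", and states that "a total of 134 participants will be required to achieve 80% power with alpha set at *p* < .05". It then allows for dropout, "Based on an estimated drop out of 30% from web-based tailored interventions to increase physical activity", and concludes that "the final target sample size of 192 participants (48 per group) will be recruited at baseline". No dropout rate by arm is given.

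The Study hypotheses section expects no change in the control group, and greater change among participants who engage more.

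**The concern.** Intention-to-treat says who is analysed and in which group. It does not say how a missing value is filled. Here the label is attached to a deterministic single imputation. There is only one post-baseline assessment, so the imputed change is zero for every dropout, and these zeros enter the primary contrast as if they had been observed.

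The two sections also treat dropouts differently. The sample-size calculation counts them as lost and plans for the full 0.28 among those who remain. The analysis brings them back with zero change, which lowers the effect being estimated unless that is what happened to them.

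Dropout could well differ by arm. Only the intervention groups receive weekly texts and prompted fortnightly sessions, which might burden participants or help to retain them. Controls are offered intervention content after the three months, which may keep them in the study. At stake are the size of the main estimate and the coverage of its interval, and in some settings the false-positive rate.

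**Working it through.** **Inputs from the protocol article:** effect d = 0.28; dropout 30%; 134 required and 192 recruited (48 per group). Allocation is equal, so pooling the intervention groups gives 144 versus 48. There is one follow-up.

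**Inputs that are assumptions:** change in the control group (c), dropout by arm (pT intervention, pC control), baseline to follow-up correlation (r), and how dropouts would have changed.

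**The plan's own figure.** 134 / (1 - 0.30) = 191.4, rounded up to 192, so the dropout inflation reproduces. Dropouts imputed to zero: 0.30 x 192 = 57.6, about 58. Whether 134 is itself adequate is a separate question and is not used here.

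**Expected estimate.** With dropout unrelated to outcome and mean changes muT and muC among completers, baseline carried forward (BOCF) estimates

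(1 - pT) x muT - (1 - pC) x muC.

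- Equal 30% dropout, true effect 0.28: 0.70 x 0.28 = 0.196, whatever the control change.
- No true effect, common change c: bias = -c x (pT - pC). At c = 0.3 and 35% versus 15%: -0.3 x 0.20 = -0.06 SD. With the rates swapped: +0.06 SD.
- No true effect and c = 0: bias is zero for any dropout split.
- True effect 0.28, c = 0.3, 35% versus 15%: 0.65 x 0.58 - 0.85 x 0.30 = 0.122.
- The same with the rates swapped: 0.85 x 0.58 - 0.65 x 0.30 = 0.298.

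The 35%/15% split keeps 30% overall (0.75 x 35 + 0.25 x 15 = 30). The swapped split gives 20% overall (0.75 x 15 + 0.25 x 35 = 20).

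**Simulation** (48 versus 144, unit-variance normal outcomes, r = 0.5, 4,000 runs). BOCF was analysed by ANCOVA and by change score, hence the ranges. The comparator is a baseline-adjusted analysis of observed data. Truth is the effect in all randomised participants.

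| Dropouts' true change | Dropout, interv./control | c | Truth | BOCF | Observed data |
|---|---|---|---|---|---|
| As completers | 30% / 30% | 0 | 0.28 | 0.19, coverage 89-91% | 0.28, coverage 95% |
| As completers | 35% / 15% | 0.3 | 0.28 | 0.12, coverage 77-80% | 0.28, coverage 95% |
| As completers | 15% / 35% | 0.3 | 0.28 | 0.30, coverage 96% | 0.28, coverage 95% |
| As completers | 35% / 15% | 0.3 | 0 | -0.06, type I error 8-9% | 0.00, type I error 5% |
| As completers | 35% / 15% | 0 | 0 | 0.00, type I error 6-7% | 0.00, type I error 5% |
| None | 30% / 30% | 0 | 0.196 | 0.20, coverage 95% | 0.28, coverage 92% |
| Half of completers' | 30% / 30% | 0 | 0.238 | 0.20, coverage 94-95% | 0.28, coverage 94-95% |

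At r = 0.8, BOCF coverage falls to 85-88% in the first row and 62-64% in the second. Type I error in the fourth row rises to 12%.

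**Power.** Under equal 30% dropout and r = 0.5, BOCF has 28-32% and the observed-data analysis 36%. If the SD of change is set so that 134 completers at 1:1 give 80%, BOCF gives 74-79%. The loss is modest because BOCF also lowers the standard error.

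**Standard errors.** Under equal dropout the model standard error (0.128) matches the empirical one (0.127), so the undercoverage there comes from the shrunken estimate. At 35%/15% with no drift the model value is slightly too small (0.127 against 0.133). When more controls drop out, it errs slightly the other way.

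**The case against.** The strongest defence is that BOCF may be closer to the truth than the alternative. The protocol itself hypothesises that greater engagement brings greater change. Dropouts are plausibly the less engaged, so they may have changed less than completers. If they stayed at baseline, BOCF is right and the missing-at-random analysis overstates the effect (0.28 against 0.196). If they made half the gain, the two err by about the same amount in opposite directions. This stands: neither assumption can be verified from the trial data.

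A reader might infer that the rule always shrinks the effect by the dropout rate, that unequal dropout always creates a false difference, or that its intervals always undercover because standard errors are too small. The documents do not support any of these. The first needs equal dropout and dropouts who would have changed as completers did. The second needs a non-zero mean change, whereas the protocol hypothesises none in controls. The third fails in several rows of the table.

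The planned completers analysis also counts. With one follow-up and complete baselines, a baseline-adjusted completers analysis is essentially the observed-data comparator used above. The article does not say that its version adjusts for baseline, and it gives neither result priority. The mitigation is therefore real but partial.

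The defence that BOCF is at least conservative does not stand. With upward drift and less dropout in the intervention arms, it favours the intervention.

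**Conclusion.** The point holds in conditional form. The protocol article fixes, without a stated reason, a zero change for an expected 30% of participants and calls this intention-to-treat.

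- If dropouts would have changed as completers did and dropout is equal, 0.28 becomes about 0.20, coverage is about 90%, and the power loss is modest.
- If dropout differs by arm and mean change is not zero, bias can go either way. It is 0.06 SD in size under no true effect with c = 0.3 and a 20-point dropout difference.
- If dropouts stay at baseline, the rule is accurate.

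Drift, dropout by arm, correlation and the dropouts' true change are all assumptions. The most adverse figures (coverage 77-80% at r = 0.5) come from one unfavourable combination of them and should not be read as the expected result.

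This should be fixed, but it does not by itself invalidate the trial. The rule is disclosed in advance and a completers analysis sits beside it. However, the article describes no other analysis that probes dropout.

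**What to change.** Make the primary intention-to-treat analysis the mixed model already planned, fitted to all randomised participants with every observed baseline and follow-up value, under missing-at-random. Alternatively, extend the chained-equations imputation already planned for other missing data to dropouts, by arm and with baseline covariates. Keep baseline carried forward as a sensitivity analysis beside a delta-adjusted one that lets dropouts do worse than missing-at-random predicts, with the adjustment allowed to differ by arm. Use the term intention-to-treat only for the set analysed, and state which analysis is primary.

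The cost is analysis wording; no data collection or sample size changes. The downside is that the primary result then rests on missing-at-random, which may be optimistic if disengaged participants are the ones who leave. The sensitivity analyses must therefore be reported with it.
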